## Stopping rules

In this minimal risk lifestyle intervention trial, it is more likely that difficulty in recruiting adequate numbers of participants will require stopping the trial than that excess adverse events will occur and require stopping the trial. However, as outlined elsewhere, we will monitor injury rates in all participants and the safety officer, together with the study investigators, will alert the IRB and the NIH if a larger than reasonably expected event rate should occur in the treatment group. Other issues relating to stopping rules for this trial include:

New Information

It is exceedingly unlikely that any new information will become available during this trial that would necessitate stopping the trial.

Limits of Assumptions

It is possible that baseline differences between the groups, excessive study dropouts and/or missing data by the interim measurement time point will limit the value of data analysis of measurements at the 3-year time point. Baseline differences will be evaluated after the first measurement time point. Given the monitoring plans outlined elsewhere in this document, it is exceedingly unlikely that there will be baseline differences between groups of any magnitude to threaten the validity of the study.

While this R01 mechanism's primary aim is to determine the feasibility and acceptability of the intervention our goal is also to obtain appropriate estimates for a larger trial. Based on a sample size of 132 participants with an expected attrition of 15% we will have sufficient power (98%) to detect an 8-pound difference SD 10.4) between the intervention and control group (secondary outcome). Alert points are set at dropout rates of 30% (low alert), 40% (mid-alert), and 50% (high alert). As shown in the table below even at a high level alert we will still have moderate power (0.87) to determine our secondary outcomes.

| Dropout Rate  Alert level | 30%  low | 40%  mid | 50 %  high |
| --- | --- | --- | --- |
| Power available | 96% | 92% | 88% |

The actions taken at each level of alert are given below:

Low to mid-level alert = Conference call between study investigators to discuss approaches to minimize further losses to follow-up/dropouts.

High-level alert = Conference call between investigators to determine further alterations of study protocol to complete the study with no further losses. In the unlikely event of a 50% dropout rate occurs prior to the 6-months measurement time point, study investigators would convene on a conference call to discuss the usefulness of continuing the study.

Limits of Rules

We acknowledge that there are other situations that could occur that might warrant stopping the trial and have a section on the safety report entitled ‘Other situations that have occurred since the last safety report that warrant discussion’ to allow for communication of concerns to the study PI, statistician, and the safety officer.

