### **6.1.2 Treatment Phase**

Eligible participants will be randomly assigned to the social network intervention or control groups in a 1:1 ratio using a numerical randomization scheme developed by the statistical team. Following randomization, participants that are randomized to the social network intervention group will complete 3 in person communication skills sessions with their social network members during weeks 3, 5, and 15. Instead of completing communication skills sessions, participants randomized to the control group will complete regular virtual lifestyle coaching sessions with the study team that consists of the following topics: Keep your health healthy (week 3), Eat well away from home (week 5), and Social Cues (Week 15). All other sessions will focus on the topics below and will be the same across both treatment groups.

Note: The weeks that are not listed in the treatment phase below are weeks that will be treatment breaks.

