## Measurement and reporting of adverse events

We plan to collect symptom data related to increased physical activity and adverse events as part of the routine coaching sessions at week 3, 4, 5, 7, 9, 11, 13, 15, and 20. We plan to present unblinded adverse events data to the study statistician, the PI, and the safety officer throughout this trial. There is some level of injury expected from individuals potentially increasing their physical activity although the recommended mode of physical activity will be walking and reducing sedentary time. In our previous RCT study of 405 adults enrolled in a lifestyle intervention study and followed over 12 months, 13 (16%) expected adverse events (were likely related to the study protocol. Among all AE's, 17 (21%) were related to musculoskeletal complaints. There were 7 (9%) cardiovascular events and 17 (21%) pulmonary events. 73% of the total adverse events (81) were rated as unlikely or unrelated to the intervention. ^28^

Definitions of expected adverse events for this study:

*Cardiovascular, pulmonary, hypoglycemia:* Adverse events will be defined as cardiovascular (MI, CVA, death), acute shortness of breath, or hypoglycemia precipitated by changes in dietary intake or the physical activity chosen for the study requiring hospitalization/emergency room visit or a physician office visit. Non-routine office visits for cardiac or pulmonary disease or diabetes are expected and not serious unless they lead to the above events.

*Major depressive episode or anxiety attack:* Infrequent likelihood. A participant may become depressed, anxious or severely embarrassed if friends/family/acquaintances find out that the person is participating in and/or not losing weight in the program. Patients have the option of not answering any questions they do not want to. As this is a voluntary study, a participant is free to withdraw from the study at any point if they feel uncomfortable or do not want to continue.

*Medication Side Effects* Infrequent risks. The study does not prescribe medication. Weight loss can cause a change in the dose of medication needed to treat common health conditions such as hypertension, diabetes and hypothyroidism. Participants will be required to communicate their participation in the study along with their weight loss to a primary care physician.

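### The rate-based harm alert covers only the treatment group, although injuries are monitored in everyone and both arms follow nearly the same diet and activity programme

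*Protocol*

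**What the plan says.** Section 15 of the protocol (Data and Safety Monitoring Plan) handles harm in several places.

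- **Stopping rules.** The surveillance is general: "we will monitor injury rates in all participants". The action is narrower: the safety officer and investigators "will alert the IRB and the NIH if a larger than reasonably expected event rate should occur in the treatment group". No number, time window or comparison defines what is reasonably expected.
- **Opening of section 15.** Excessive adverse events and any serious adverse event are to be reported promptly to the NIH and the IRB. No arm is named and no threshold is given.
- **Measurement and reporting of adverse events.** The background comes from an earlier trial: "In our previous RCT study of 405 adults enrolled in a lifestyle intervention study and followed over 12 months". The text gives 13 (16%) events likely related to the protocol, then "Among all AE's, 17 (21%) were related to musculoskeletal complaints" and "There were 7 (9%) cardiovascular events and 17 (21%) pulmonary events". The total appears last: "73% of the total adverse events (81) were rated as unlikely or unrelated to the intervention".

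On the programme itself, section 6.1.2 replaces the control topics at weeks 3, 5 and 15 with communication training in the intervention arm, and adds: "All other sessions will focus on the topics below and will be the same across both treatment groups". Section 1 gives 66 index participants per arm and 15 sessions in each. Section 7.9 has both arms treated for 24 weeks.

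**The concern.** Within one sentence the plan watches everyone but alerts on one arm. In many trials that would be reasonable, because the control arm is not exposed to the hazard. Here it is. The expected physical harms (musculoskeletal injury, cardiovascular and pulmonary events, hypoglycaemia) are tied in the protocol to dietary change or to the chosen physical activity, and both arms receive that coaching. What only the intervention arm receives is communication training with network members.

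Two things are at stake. An unexpected cluster of injuries among controls would not meet the alert as worded. And if the shared programme does cause more injuries than expected, the alert counts only about half of the relevant events, so it is slower and less likely to respond. With a handful of events expected per arm, that loss matters.

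A smaller issue is the benchmark. The background percentages follow a sentence that names 405 adults, but they are shares of 81 events. A reader who wants an expected rate has to derive it.

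**Working it through.** **1. Scope of the passages, side by side**

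| Place in the protocol | Who is covered | Threshold |
|---|---|---|
| Section 15, opening | No arm restriction | None stated |
| Section 15, Stopping rules: monitoring | All participants | None stated |
| Section 15, Stopping rules: rate alert to IRB and NIH | Treatment group | Reasonably expected, no number |
| Sections 13.1.4 and 13.2.1, AEs and SAEs to IRB | All on study | IRB policy |

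The protocol uses the term treatment group loosely: section 6.1.2 calls both arms treatment groups, while section 7.9 sets control against treatment. In the stopping rules the natural reading is the intervention arm.

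**2. Shared exposure**

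15 sessions per arm, of which 3 differ (weeks 3, 5, 15): 15 − 3 = 12 sessions are common to both arms.

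**3. Reproducing the printed percentages**

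| Category | Count | Printed | Count/81 | Count/405 |
|---|---|---|---|---|
| Likely related | 13 | 16% | 16.0% | 3.2% |
| Musculoskeletal | 17 | 21% | 21.0% | 4.2% |
| Cardiovascular | 7 | 9% | 8.6% | 1.7% |
| Pulmonary | 17 | 21% | 21.0% | 4.2% |

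All four figures reproduce as shares of 81 events and none as a proportion of 405 adults.

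**4. Expected musculoskeletal counts here**

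Assumptions: constant rate over the 12 months, ascertainment similar to the earlier trial, and full 24-week follow-up.

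Expected count = n × (17/405) × (24/52).

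- One arm: 66 × 0.0420 × 0.4615 = 1.28
- Both arms: 132 × 0.0420 × 0.4615 = 2.56

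**5. What the one-arm restriction costs**

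Take an illustrative rule (not in the protocol): alert at the smallest count whose Poisson tail probability under the expected mean is at most 5%, looked at once at the end.

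| Data used | Mean expected | Alert at | False-alert probability | Mean under 3-fold excess | Detection probability |
|---|---|---|---|---|---|
| Intervention arm only | 1.28 | 4 or more | 0.041 | 3.84 | 0.53 |
| Both arms pooled | 2.56 | 6 or more | 0.046 | 7.67 | 0.78 |

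The excess is assumed equal in both arms, as it would be if the shared programme caused it. For a two-fold excess the detection probabilities are 0.26 and 0.40.

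**6. Sensitivity to ascertainment**

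If this trial captured events at twice the earlier rate, and the expectation were set to match (2.56 per arm, 5.11 pooled), detection of a three-fold excess would be 0.78 in one arm and 0.94 pooled. At half the earlier rate (0.64 and 1.28) it would be 0.30 and 0.53. Pooling helps in each case.

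**7. False alerts if each arm and the pool are all checked**

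Using the thresholds in step 5 (4 or more in either arm, or 6 or more pooled), the probability of at least one false alert is 0.09 for this one event category at a single look.

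**The case against.** Four arguments deserve weight.

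**Controls are not unprotected.** A reader might infer that no safety signal can ever arise for half of the randomised participants. The documents do not support that. Sections 13.1.4 and 13.2.1 send AEs and SAEs to the IRB under its policy. Section 14 requires 7-day reporting of related problems that are unexpected in nature, severity or frequency and suggest greater risk. The opening of section 15 has no arm limit, and unblinded adverse event data go to the statistician, the principal investigator and the safety officer throughout. The safety report also has an open item for other situations. This stands, and it narrows the point to the rate alert.

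**A shared hazard would also show in the intervention arm.** True, so the alert is not blind to it. What remains is the loss of sensitivity in step 5, plus any cluster confined to controls, which might be chance but would still merit a look.

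**The percentages are not the benchmark.** A reader might infer that taking 21% as a rate sets the tolerated level five times too high, or about eleven times after scaling to 24 weeks. That needs a misreading the text does not invite: the musculoskeletal figure is introduced as a share of all events, the counts are printed, the total of 81 is given, and the stopping rules do not name these figures as limits. Only the request for clearer labels survives.

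**The working limits may lie elsewhere.** The safety officer uses an attached checklist to judge corrective action and stopping-rule violations. It is not shown and may hold thresholds, so the absence of a number is no finding. It would not, however, change what the stopping rules say about scope.

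**Conclusion.** The point holds in a limited form. The rate alert in the stopping rules is narrower than both the monitoring it rests on and the reporting promised at the start of section 15, and the restriction does not suit a design in which 12 of 15 sessions are the same in both arms. Individual events in controls are still reported, so the gap is one of rate-based detection.

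Its size, on the sponsor's own earlier figures, is a fall in the chance of detecting a three-fold musculoskeletal excess from about 0.78 (pooled) to about 0.53 (intervention arm only). That rests on a constant event rate, similar ascertainment, full 24-week follow-up, an equal excess in both arms, and an illustrative 5% rule that the protocol does not contain. Ascertainment is the weakest of these: symptoms are collected at nine coaching sessions here, and the earlier trial's methods are not described. The direction of the result does not depend on it.

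The correction is worth making because it concerns safety and costs almost nothing.

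**What to change.** 1. Reconcile the opening of section 15 with its stopping rules, so that the rate alert to the IRB and NIH covers each arm and all 132 index participants pooled.
2. In the section on measuring and reporting adverse events, label the 16%, 21%, 9% and 21% as shares of the 81 events.
3. In each safety report, print observed counts by arm and pooled beside expected counts per participant-time from the sponsor's own data. For musculoskeletal events this is about 1.3 per 66 and 2.6 per 132 over 24 weeks, adjusted for the follow-up accrued at the time of the report, with the constant-rate and ascertainment assumptions stated.
4. If the safety officer's checklist already holds limits, refer to it from the stopping rules and check that its scope agrees.

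The cost is a wording change and a line in an existing report. No new data are needed, since unblinded adverse events already reach the people concerned. The downside is an occasional false alert (about 0.09 for one event category under the illustrative thresholds, more with several categories or repeated looks). Each would cost a review by the safety officer and possibly a notice to the IRB and NIH that proves unnecessary.

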# Appendix A – Table 1: Schedule of Assessments

[figure not shown]

# Appendix B – Communication Skills session outline

| **SUMMARY OF ROBUST INTERVENTION SESSIONS WITH SOCIAL NETWORK MEMBERS** | | |
| --- | --- | --- |
| **Timepoint** | **Activity** | **Outcome/ Assessment** |
| Baseline – Social Network Member | - Completion of baseline survey - Program overview regarding the role of the social network member and available resources - Program overview of what the index participant will be doing - ***Assignment 1****:* Before the week 3 session instruct index participants to think about the type of the support they would like from the social network members during the program | - REDCAP survey of daily PA/SA exercise implementation during weeks 1-2 |
| Week 3 | - Coaching session will introduce elements of communal coping and review the definitions of positive affect and social undermining.   - Coach reviews ways in which social undermining can discourage positive eating and physical activity - Participant and social network member to set supportive SMART goal - ***Assignment 2:*** Participant and social network member to work on adhering to their self-selected supportive SMART goal and write down any problems with adhering | - Completion of a self-reported measure of adherence to enacting the supportive SMART goal by the alter and receipt of the SMART goal by the index participant |
| Week 5 | - Review of how to recognize social undermining and how to create positive affect in regards to engaging in positive eating & physical activity behaviors. - Coach will discuss how to use the 5 steps to problem solving in order to avoid social undermining and to encourage healthy eating out habits. | - Completion of a self-reported measure of adherence to enacting the supportive SMART goal by the alter and receipt of the SMART goal by the index participant |
| Week 15 | - Discuss usage of the positive affect and communal coping skills created to learn how to address social cues that trigger negative eating and physical activity behaviors and complete accompanying in session activity. - ***Assignment 3:*** Index participant will be asked to complete the handout on dealing with problem social cues and plan to review the responses with their social network members | - Self-reported count of the number of people that were engaged in a risk communication conversation since week 5 - Completion of a self-reported measure of adherence to enacting the supportive SMART goal by the alter and receipt of the SMART goal by the index participant |
| Week 24 | - Completion of closeout survey | - REDCAP |
